#### Related analysis

2.29.3

The significant brain regions detected after treatment in the observation group and the control group will be analyzed by Pearson correlation analysis with the results of neuropsychological scales and serum biomarkers by SPSS software. The statistical significance threshold was set at *P* = .05. Only correlations index of *P* < .05 was considered as valid correlations.

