**Discussion::**

This trial can clarify the effect of acupuncture-rehabilitation therapy on hippocampal volume and its intervention mechanism on oxidative stress injury in VCI patients with T2DM, and clarify the scientific connotation of its neuroprotective mechanism in the VCI patients with T2DM, in order to provide a theoretical basis for the clinical application of acupuncture-rehabilitation therapy in the treatment of VCI.

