### Trial design

2.2

This is an outcome assessor- and data analyst-blinded, partial randomized controlled trial conducted at the Second Affiliated Hospital of Heilongjiang University of Chinese Medicine from January 1, 2021 to December 31, 2023. A total of 80 subjects who met the inclusion criteria including 25 healthy volunteers, 25 T2DM patients with normal cognitive function, and 30 patients with VCI combined with T2DM were recruited into the study. First, they were scanned by fMRI, through the calculation and analysis of VBM indexes, the changes in hippocampal volume and function in the 3 groups of patients were compared to determine the difference between type 2 diabetes patients and healthy volunteers, correlation between hippocampal structural and functional changes in patients with normal cognitive T2DM and VCI patients with T2DM. Then, 30 VCI patients with T2DM were randomly divided into the experimental group and the control group, the control group was given routine drug therapy to control blood glucose and improve cognitive function, the experimental group was given acupuncture-rehabilitation therapy on the basis of the control group. The primary outcomes were obtained by VBM calculation and serum biomarkers (SOD, MDA, BDNF) detection, and the secondary outcome indexes were assessed by neuropsychological scales such as Montreal Cognitive Assessment (MoCA), Wechsler Memory Scale IV edition (WMS-IV), FIM, among others. Serum biological indicators and neuropsychological scale will be conducted before treatment, as well as 4 weeks, 8 weeks, and 12 weeks after treatment respectively, fMRI scan will be conducted before treatment and 12 weeks after treatment respectively, to observe the intervention effect of acupuncture-rehabilitation therapy on cognitive function of VCI patients with T2DM. Figure 1 and Table 1*present the technology roadmap and clinical observation flow charts, respectively.*

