### Secondary outcome measures

2.24

**MoCA Scale:** The MoCA is presently recognized as one of the cognitive impairment screening scales, which mainly includes attention, executive function, memory, speech, visual space structure, abstract thinking, calculation ability, and other aspects of screening.^[8]^ Compared with the MMSE, MoCA has better sensitivity and specificity for mild cognitive impairment. The total score of MoCA is 30 points. If the subject has been in education for ≤12 years, 1 point is added. A score <26 points is considered to have cognitive impairment.

**WMS-IV:** The Wechsler Memory Scale (WMS) is a set of tests to assess various memory abilities and working memory. It can provide detailed evaluation of clinical memory function for patients suspected of having memory deficits, psychiatric diseases, or developmental disabilities. The WMS was released in 1945 and has been revised to the fourth edition(WMS-Fourth edition) in 2008,^[9]^ WMS-IV has adjusted and improved the structure and content of the original scale, extended the age of the subjects to 16 to 90 years’ old, and added 4 subscales (concise cognitive status assessment, graphic recognition, spatial superposition, symbol breadth), and provide auditory memory, visual memory, visual working memory, instant memory and delayed memory, and total memory quotient to explain the individual's memory ability.^[10]^ Not only to assess memory function, but also to make a brief assessment of cognitive function status.

**FIM:** The FIM is a comprehensive and objective assessment method that reflects the patient's activities of daily living. It selects the most common and useful 18 functional assessment items (including 6 self-care activities, 2 sphincter control, 3 transfers, 2 walking, Communicate 2 items and 3 social cognition items), and determine the appropriate grading scoring method (each item is divided into 7 levels, the highest score is 7 points, the lowest score is 1 point, the total score is the highest 126 points, the lowest 18 points. The higher the score, the better the level of independence, the worse on the contrary.). This scale can comprehensively reflect the patient's function and independent living ability, evaluate and compare the severity of the patient's disability, predict the rehabilitation consequences, formulate rehabilitation goals, select treatment plans, and evaluate the rehabilitation efficacy.

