#### Statistical processing and result presentation of brain function data

2.29.2

Statistical analysis is carried out by using DPASFA, SPM12, Xjview, Rest, and other software based on MATLAB platform.

The values of VBM, ReHo, and FC of healthy volunteers, T2DM cognitive normal group, and VCI group with T2DM were analyzed by ANOVA, with sex, age and years of education as covariates. The test level was set to: cluster level *P* < .05 (FWE or FDR correction). If *P* < .05 and could at least pass the FDR correction, there was a significant difference between the 2 groups of patients and healthy volunteers, which was statistically significant.

In the VCI group with T2DM, the data of VBM, ReHo, and FC in the experimental group and the control group were compared by double-sample *t* test. Paired-sample *t* test was used for intra-group comparison between the 2 groups before and after treatment. The test level was set as: cluster level *P* < .05 (FWE or FDR correction). If *P* < .05 and could at least pass the FDR correction, it was considered that there was a significant difference between the experimental group and the control group, which was statistically significant.

The statistical results were presented by Xjview and Mricron software.

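### Related analysis accepts every uncorrected P<.05 correlation between significant brain regions and at least six measures, and does not say how treatment arm is handled

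*Protocol article*

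**What the plan says.** Section 2.29.3 (Related analysis) takes as input the regions that came out significant: "The significant brain regions detected after treatment in the observation group and the control group will be analyzed by Pearson correlation analysis". They are paired "with the results of neuropsychological scales and serum biomarkers by SPSS software". The acceptance rule is "Only correlations index of *P* < .05 was considered as valid correlations".

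The scales are "Montreal Cognitive Assessment (MoCA), Wechsler Memory Scale IV edition (WMS-IV), FIM, among others" and the markers come from "serum biomarkers (SOD, MDA, BDNF) detection" (both section 2.2). Section 2.24 adds that the WMS-IV can "provide auditory memory, visual memory, visual working memory, instant memory and delayed memory, and total memory quotient", which is six indices from one scale.

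The regions come from section 2.29.2, where "the data of VBM, ReHo, and FC in the experimental group and the control group were compared by double-sample *t* test" and paired tests are run within each arm. Those maps need FWE or FDR correction at cluster level. Covariates (sex, age, education) are named only for the three-group ANOVA. Section 2.29.3 names no correction, no arm term and no covariate. It does not say whether the two arms are combined.

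**The concern.** Two problems follow from the written rule.

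- **Multiplicity.** Each region is tested against at least six measures at .05, and each result below .05 is accepted individually. The correction required for the maps stops at the maps. This holds whether the arms are pooled or analysed separately.
- **Treatment arm.** If all randomised patients enter one plain Pearson correlation, two variables that both respond to treatment will correlate because the arms have different means, even if patients within an arm show no association.

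The abstract says the trial can "clarify the scientific connotation of its neuroprotective mechanism in the VCI patients with T2DM". A correlation between a brain region and a cognitive score or oxidative-stress marker, reported as valid, would naturally be read as support for that statement. The rule as written does not separate such a link from chance or from a shared treatment effect.

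**Working it through.** Section 2.29.3 gives no sample size, power or number of tests, so its only figure is the .05 threshold (taken as two-sided). There is no stated result to reproduce.

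**Inputs from the protocol**
- Measures: MoCA, WMS-IV, FIM, SOD, MDA, BDNF = 6. With all six WMS-IV indices: 1 + 6 + 1 + 3 = 11.
- Arm size: 15 enrolled, 13 before the dropout allowance (section 2.5). These are used here only as counts.
- MoCA improvement at 4 weeks: 3.13 (SD 0.75) versus 1.53 (SD 0.33) (section 2.5). The difference is 1.60. The root-mean-square SD is √[(0.75² + 0.33²)/2] = 0.579. The standardised difference is 1.60/0.579 = 2.76.

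**Assumptions**
- The number of surviving regions (1, 3 or 5).
- Every standardised arm effect other than the 2.76, because the protocol gives none for a brain region or a serum marker. The 1.33 SD is roughly what 13 per arm detects with 90% power; it is not an expected effect.

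**Step 1: multiplicity.** With independent tests and no true correlation, P(at least one false acceptance) = 1 − 0.95^m.

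| Regions | m, one set | Chance | m, each arm separately | Chance |
|---|---|---|---|---|
| 1 | 6 | 26.5% | 12 | 46.0% |
| 3 | 18 | 60.3% | 36 | 84.2% |
| 5 | 30 | 78.5% | 60 | 95.4% |

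The expected number of false acceptances is 0.05m, for example 0.9 for 18 tests and 1.5 for 30. With 11 measures and 3 regions, m = 33 and the chance is 81.6%. Correlated measures lower all these figures.

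**Step 2: arms pooled.** With zero correlation within arms, equal arms and standardised arm effects d1 and d2, the induced correlation is

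r = (d1·d2/4) / √[(1 + d1²/4)(1 + d2²/4)].

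- d1 = d2 = 1.33: 0.442/1.442 = 0.31.
- d1 = 2.76, d2 = 1.5: 1.035/√(2.904 × 1.5625) = 0.49.

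With 30 patients pooled, |r| above 0.361 gives P<.05. Simulation (20,000 runs, 15 per arm, zero within-arm correlation) gives the share of single tests that pass:

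| Region effect (SD) | Outcome effect (SD) | Pooled | Adjusted for arm |
|---|---|---|---|
| 1.2 | 0 | about 5% | about 5% |
| 1.2 | 0.8 | 18% | about 5% |
| 1.33 | 1.33 | 41% | about 5% |
| 1.5 | 2.76 | 85 to 86% | about 5% |

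**Step 3: arms separate.** There is no arm confounding and the single-test rate stays at about 5%, but the tests double (Step 1). The critical |r| is 0.514 with n = 15 and 0.553 with n = 13, so any correlation that passes is necessarily large and tends to overstate the true one.

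**Step 4: is arm adjustment enough?** No. With arm removed, the simulated chance of at least one false acceptance at uncorrected .05 is still 26 to 28% for one region and 60 to 61% for three regions, with six measures. Both changes are needed.

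**The case against.** The strongest reply is that much of this is conditional and could be settled in the statistical analysis plan that section 2.28 says a third party will write. Pooling is not stated. Section 2.29.2 includes within-arm tests, so correlating within each arm is an equally open reading, and then arm confounding disappears. This stands, and the arm part is therefore put as a condition. It does not reach the acceptance rule, which the protocol itself fixes and a later plan would have to reverse.

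The effect sizes are also assumptions. The 2.76 SD is a 4-week MoCA figure, while the repeat scan is at 12 weeks. That stands too, which is why a range starting at 5% is given. Likewise, few or no regions may survive correction with 15 per arm; one region gives 26%, not 79%.

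Three stronger readings are tempting, and the documents do not support them:

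- **That such correlations arise from arm and multiplicity alone.** They can. Whether they do depends on pooling and on the outcome also differing by arm.
- **That choosing regions for significance is circular.** The regions are chosen on treatment effect, not on their correlation with scores. An arm-adjusted correlation in a selected region stays near 5%. Selection does harm only when arms are pooled and the outcome also differs by arm.
- **That the mechanism claim rests on these correlations.** The objectives (section 2.1) tie mechanism to hippocampal volume and oxidative stress, and VBM and the serum markers are primary outcomes compared between arms. The correlations are supporting evidence.

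**Conclusion.** The point holds in this limited form. The written rule accepts uncorrected P<.05 results across all pairs of significant regions and at least six measures. That carries roughly a 26% to 79% chance of at least one false acceptance for one to five regions, or 46% to 95% if run by arm. These figures assume independent tests and an assumed number of regions.

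Separately, the section does not say how arm is handled. If arms are pooled, the single-test error runs from 5% (no arm effect on the outcome) to about 86% (the MoCA effect from section 2.5 with an assumed 1.5 SD region effect). If they are not pooled, this part falls away and the multiplicity worsens.

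The primary arm comparisons are unaffected. The matter should be corrected before analysis because accepted correlations would be read as evidence of mechanism.

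**What to change.** - Correlate change from baseline to 12 weeks in each region with change in each measure, pooling the arms and using partial correlation adjusted for arm. If separate analysis by arm is intended, say so and count both sets of tests in the correction.
- Apply FDR across all region-by-measure pairs, after stating which WMS-IV indices enter.
- Report every r with its confidence interval, whether or not it passes.
- Replace the wording about valid correlations with a statement that the analysis is exploratory and does not establish mechanism.
- Optionally, add the hippocampus, which the objectives name, as a prespecified region alongside the whole-brain findings. It need not replace them, since the Discussion gives a reason for preferring a whole-brain method.

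The cost is wording and analysis time, with no new patients, visits or scans. The drawback is that fewer correlations will be called significant, and with about 30 patients perhaps none.

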## Discussion

3

The onset of vascular cognitive impairment is hidden, which is characterized by the decline of learning, memory, visual-spatial, understanding, executive and other abilities decreased in varying degrees after suffering from cerebrovascular disease, which seriously interferes with the patients’ daily life and brings heavy pressure and burden to the patients’ families and society.^[1]^ DM, especially T2DM, is an independent risk factor for VCI. Long-term chronic hyperglycemia can stimulate capillary basement membrane thickening and promote atherosclerosis. In addition, T2DM patients are often complicated with lipid metabolic disorders, high blood viscosity and slow blood flow, which can eventually lead to a decrease in cerebral blood flow, resulting in functional disorders in cognitive-related brain areas such as hippocampus, para-hippocampal gyrus gray, superior temporal gyrus, angular gyrus gray, and so on, so as to accelerate the occurrence of cognitive impairment in T2DM patients.^[11]^ Therefore, T2DM can not only lead to cerebrovascular disease, increase the risk of stroke, but also directly lead to cognitive impairment. Most cross-sectional studies have found that the cognitive function of newly diagnosed diabetic patients began to decline: the MMSE score decreased 0.06 points for every 1mmol/L increase in blood glucose (*P* <.01).^[12]^ For every 1% increase in HbA1C, the standardized Cognitive Assessment Screening Instrument score decreases by 0.06% (95% confidence interval −0.101 to −0.018).^[13]^ Insulin resistance indicates a decline in cognitive ability mainly in the field of memory in patients with prediabetes.^[14]^ Diabetes can also have a synergistic effect with hypertension and heart disease, increasing the risk of cognitive impairment in patients with cerebrovascular disease.^[15]^

Acupuncture-rehabilitation therapy is a new treatment system for stroke dysfunction, which has been studied and summarized continuously by [name] of Heilongjiang University of Traditional Chinese Medicine after years of experimental and clinical research, and has standardized clinical operation techniques. This method organically combines the cluster needling at scalp points with modern rehabilitation technology to maximize their advantages. On the one hand, the acupuncture effect of the head acupoint prickling can stimulate the cerebral cortex through the skull, regulate the function of the cerebral cortex and reach the focus of responsibility, improve brain function under pathological condition.^[5]^ On the other hand, modern rehabilitation techniques promote the “sprouting” of the damaged brain synapses and the establishment of collateral circulation, so as to compensate the damaged brain tissue around the focus and even the contralateral brain tissue, and give full play to the “plasticity” of the brain. For cognitive dysfunction, acupuncture-rehabilitation therapy means the cluster needling at scalp points and cognitive function training combined with a combination of a treatment.

VBM is an automatic, comprehensive and objective analysis technique for MRI of brain structures based on voxels. The traditional functional magnetic resonance measurement method is to measure and calculate around a pre-selected area of interest, which has the disadvantages of time-consuming, strong subjectivity, poor reproducibility, and inability to perform whole-brain analysis. The VBM can measure and compare the whole brain, directly analyze the original data, without making a priori assumptions, and can quantitatively detect the volume difference of the brain tissue, without subjective influence of the researcher, with automatic, comprehensive and objective and repeatability and other advantages. Some studies have shown that the structural network of patients with T2DM has been significantly damaged at the whole brain and regional level. Mild cognitive impairment patients with T2DM showed more severe impairment of whole brain network efficiency, as well as lower node efficiency and reduced connectivity in multiple regions such as the limbic system, basal ganglia and several cortical structures. In addition, subnetwork damage in patients with T2DM-MCI is characterized by cortical-marginal fibers, as well as commissural fibers and pathways in the frontal, temporal and occipital lobes. The global and node parameters of these changes are significantly related to the cognitive function of patients with T2DM-MCI.^[16]^ Since the slow and hidden decline of cognitive function in patients with T2DM, the detection of blood perfusion at the voxel level of the whole brain will provide sensitive and specific imaging indicators for the early diagnosis and treatment of cognitive impairment, especially for preclinical cognitive impairment. Chen et al^[17]^ found that the volume of temporal lobe, cingulate gyrus and prefrontal cortex in patients with T2DM was significantly smaller than that in normal subjects by VBM analysis. Wu et al^[4]^ found that the volume atrophy of gray matter in different brain regions of T2DM patients with cognitive impairment was higher than that of T2DM patients without cognitive impairment, especially in the middle temporal gyrus and hippocampus. Previous studies also showed that patients with diabetes were positively correlated with the severity of hippocampal atrophy and global brain atrophy (rs = 0.69, *P* < .0001).^[18]^ All the above studies have shown that the changes in the volume of some brain regions are significantly correlated with the cognitive impairment caused by T2DM. However, further studies are needed to confirm whether the occurrence of cognitive impairment is the result of the changes in the volume of a single brain region or the combined effects of the changes in the volume of multiple brain regions.

As mentioned above, oxidative stress plays an important regulatory role in the occurrence and development of diabetes mellitus and the cognitive impairment caused by it. The mechanism may be as follows: activate pancreatic β-cell NFκB signaling pathway, cause cell inflammation, induce cell apoptosis, and inhibit insulin secretion; acts on insulin signaling pathways such as InsR, IRS, PI3K, Akt, GLUT, and induces insulin resistance in liver, muscle, and adipose tissue; the injury causes the accumulation of advanced glycation end products and promotes the occurrence and development of late complications of T2DM.^[19]^

The balance of oxidation and antioxidants in brain plays an important role in maintaining cognitive function. When the level of oxidative stress in the brain is enhanced, excessive oxygen free radicals cause damage to brain cells, resulting in cognitive impairment. Hyperglycemia leading to excessive production of free radicals is the main mechanism of diabetes induced cognitive impairment. Hyperglycemia and the production of free radicals and reactive oxygen species may cause damage to multiple regions of the brain, which may be the pathological basis of cognitive impairment. The main markers of oxidative stress are free radicals. The common indicators of anti-oxidative stress include SOD, MDA, among others.

The BDNF is a growth factor belonging to the neurotrophic family and plays an important role in the nervous system. It was first discovered in pig brain by Yves-Alain Barde and his colleagues. Because it can promote the growth, reproduction, regeneration, and repair of injured neurons, mainly for a wide range of neuroprotective and neurotrophic effects, it is of great significance for the survival of neurons, the maintenance of normal function and the repair after injury, so it is mainly expressed in the central nervous system, especially in the cortex and hippocampus. A meta-analysis showed that patients with cognitive impairment may be associated with a reduction in peripheral BDNF.^[20]^

Therefore, this study intends to use VBM as the main analysis method and SOD, MDA and BDNF as the main observation indexes to explore the effects of acupuncture-rehabilitation therapy on hippocampal volume of VCI patients complicated with T2DM from the perspective of imaging and serology, as well as the intervention mechanism of oxidative stress injury in peripheral blood serum. This study provides a reliable experimental basis for the treatment of VCI combined with T2DM by acupuncture-rehabilitation therapy, and clarifying the scientific connotation of its neuroprotective mechanism, in order to provide a theoretical basis for the clinical application of acupuncture-rehabilitation therapy in the treatment of cognitive impairment.

### Dissemination policy

3.1

After study completion, the researchers will submit the final data to the National Natural Science Foundation of China in the form of a research report. The findings will be shared with healthcare professionals, the general public, and relevant organizations through the publication of manuscripts and conference presentations.

